### 2.9. Statistical Considerations

We conducted a two-factor analysis of variance with group (intervention and control groups) and time (pre-intervention and post-intervention) as factors to examine the relationship between the scores of each measurement item in the intervention and control groups. Using path analysis, we plan to conduct an exploratory analysis to investigate the relationship between each measurement item.

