### 2.6. Protocol

The design of this study is illustrated in Figure 2. First, we explained the contents of this study to the participants and obtained their informed consent. We then administered a pre-intervention baseline test to the participants. In this test, we measured cognitive function, body composition, and psychological function. The participants were then randomly divided into the natural reduced water group and tap water group, and the intervention was conducted for 6 months. During the intervention period, participants consumed 1 L of each group’s water daily and wrote down their intake on a list. We would have preferred to set the daily consumption of water to 2 L as in previous studies of Hita Tenryosui water [4], but considering the risk of hyponatremia in internal discussions, we decided to set the amount as 1 L per day. The participants were blinded so that they could not tell which water they were drinking. After the 6-month intervention, a post-intervention examination was conducted. We administered a pre-test and post-test before and after the 6-month period, drawing on other intervention studies of cognitive function [17,18]. This study will investigate the maintenance or improvement of cognitive function in healthy elderly people, not in people with dementia or other illnesses. In addition, previous studies have shown significant improvement in cognitive function in a 6-month intervention study [17,18]. The content of the post-intervention test was the same as that of the pre-intervention test. After the post-intervention test, the participants in the natural reduced water group had a follow-up test 6 months later (12 months after the start of the intervention) and were told not to drink the natural reduced water until the follow-up test. The participants in the tap water group were asked if they wanted to drink natural reduced water, and those who wanted to could drink the same amount as the natural reduced water group after the post-intervention test. Data from people whose water intake is less than 90% of the total will be excluded as dropped data. We will also exclude people who become unable to drink water during the course of the intervention or who start taking medications that meet the exclusion criteria.

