### 2.8. Sample Size

Assuming a significance level (α) of 5%, the effect size at 0.6, and a power of test (1 − β) of 80%, which are all “moderate” levels according to Cohen, the required number of participants was 34 in each group. Six months of intervention, assuming a drop rate of 10%, would require approximately 38 participants, for a total of 76 recruits. We added two more people to each group in case of unforeseen circumstances.

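### The group-by-time ANOVA tests the water effect as a change score; adjusting the 6-month score for baseline is more precise and needs no extra data

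*Protocol article*

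**What the plan says.** Section 2.9 of the protocol article fixes the main analysis for each measurement item: "We conducted a two-factor analysis of variance with group (intervention and control groups) and time (pre-intervention and post-intervention) as factors". The stated aim is to relate the scores in the two groups. Baseline adjustment is not mentioned.

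Section 2.6 gives the order of events: consent, baseline test, random division into groups, 6 months of water, post-test. It adds: "The content of the post-intervention test was the same as that of the pre-intervention test".

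Section 2.8 sizes the trial with a 5% significance level, "the effect size at 0.6" and power "of 80%, which are all “moderate” levels according to Cohen", concluding that "the required number of participants was 34 in each group". A 10% loss brings this to 38 per group, and then: "We added two more people to each group in case of unforeseen circumstances". That makes 40 per group recruited. The section does not say whether the test is one- or two-sided, whether 0.6 is in units of the SD of the score or of the change, or what pre-post correlation is expected.

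**The concern.** A two-factor ANOVA with group and time yields three F-tests, and they do not answer the same question.

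- **Group by time.** This is the randomised comparison. With two time points it equals a two-sample test of the change scores.
- **Group.** This compares the average of the pre and post scores. The pre score was taken before anyone drank study water, so the term carries only half of any effect.
- **Time.** This pools both arms. Identical test content at both visits can produce a retest gain in both arms, which says nothing about the water.

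The interaction is a valid test, but subtracting the baseline is generally not the most precise way to use it. Subtraction fixes the coefficient of baseline at 1, whereas a regression estimates it. What is at stake is precision in a small trial, plus a smaller risk that a main effect is quoted as a result.

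**Working it through.** **Inputs.** From section 2.8: effect size 0.6, alpha 5%, power 80%, 34 per group required, 40 per group recruited, 10% loss. From section 2.6: one pre and one post measurement, baseline before randomisation. Analysed number: 40 × 0.9 = 36 per arm. *Assumptions, not in the article:* r = 0.3, 0.5 and 0.7; equal SD σ at both visits; a two-sided test unless stated otherwise; both scales for d.

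**1. The plan's own figure.** For two means, n per group = 2(z_α + z_β)²/d².

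- One-sided 5%: 2(1.645 + 0.842)²/0.36 = 34.35, close to the stated 34.
- Two-sided 5%: 2(1.960 + 0.842)²/0.36 = 43.6, so 44 (45 by the t-test). With 34 per group, t-test power would be 68%.

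The stated 34 therefore matches a one-sided calculation, although no one-sided test is declared.

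**2. Variance of the treatment effect, n per arm.**

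- Interaction (change score): (2σ²/n) × 2(1−r)
- Baseline-adjusted model: (2σ²/n) × (1−r²)
- Ratio: (1−r²)/[2(1−r)] = (1+r)/2, which is 0.65, 0.75 and 0.85 at r = 0.3, 0.5 and 0.7

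The ratio depends on neither sidedness nor the scale of d. If the SDs differ (σ₀ before, σ₁ after), the change variance minus the adjusted variance is (σ₀² + σ₁² − 2rσ₀σ₁) − σ₁²(1−r²) = (σ₀ − rσ₁)². This is never negative, so the direction holds, although the ratio is then no longer exactly (1+r)/2.

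**3. Power with d = 0.6 on the score SD** (noncentral t, 36 per arm, two-sided 5%). Effective d is 0.6/√(2(1−r)) for the interaction, 0.6/√(1−r²) for the adjusted model (one degree of freedom fewer) and 0.3/√((1+r)/2) for the group main effect.

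| r | Interaction: d, power | Adjusted: d, power | Group main effect: d, power |
|---|---|---|---|
| 0.3 | 0.507, 56% | 0.629, 75% | 0.372, 34% |
| 0.5 | 0.600, 71% | 0.693, 83% | 0.346, 31% |
| 0.7 | 0.775, 90% | 0.840, 94% | 0.325, 28% |

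**4. Power with d = 0.6 on the change SD.** The interaction has 71% at every r. The adjusted model has effective d = 0.6/√((1+r)/2) = 0.744, 0.693 and 0.651, giving 88%, 83% and 78% at r = 0.3, 0.5 and 0.7.

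**5. The same comparison one-sided at 5%,** d on the score SD: 69% to 84%, 81% to 90% and 95% to 97%.

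**6. Time main effect.** Suppose there is no treatment difference and both arms gain 0.3 SD from retesting (an assumed figure). With 34 per arm, two-sided, this term is significant with probability 68% at r=0.5 and 88% at r=0.7.

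**The case against.** The strongest reply has four parts.

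*The planned test is sound.* Under randomisation the change-score comparison is unbiased and has the right error rate. A reader might infer that the ANOVA throws the baseline away. It does not: the interaction uses baseline, only less efficiently, and the loss shrinks as r approaches 1. This part stands.

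*The power argument rests on unstated inputs.* A reader might infer that the trial is short of 80% power and that adjustment restores it. The article does not support that. If the test is one-sided, 34 per group is about right. If d is on the score SD and r is 0.7, the interaction already has 90%. If r is 0.3 on that scale, adjustment reaches only 75%, and if d is on the change SD with r at 0.7, only 78%. This part stands as well. It limits the claim about power but not the variance ratio.

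*The article is condensed.* Not naming the interaction, or not calling time a within-person factor, is detail that a full protocol or analysis plan may supply. That is fair, and the silence alone would not be a finding. One could also read the wording as an ANOVA that ignores the pairing. However, the same people are tested before and after and time is made a factor, so a mixed-design ANOVA is the natural reading. Nor does any section say that a main effect will be taken as efficacy.

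*The text is in the past tense.* If the ANOVA has already been run, changing the model is more than a change of wording. The fix allows for this.

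None of this defends the change score against baseline adjustment, and the ANOVA is a method the article states, not one it leaves open.

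**Conclusion.** The point holds as a matter of efficiency and of which term is read. The article chooses an analysis whose one relevant test is a change-score comparison, where a valid and more precise test is available from the same data. With equal SDs the variance falls to (1+r)/2 of its value, that is by 35%, 25% and 15% at r = 0.3, 0.5 and 0.7.

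The gain in power depends on assumptions. Over those values of r, with 36 per arm and a two-sided test, it is about 19, 12 and 4 percentage points if d is on the score SD, and about 17, 12 and 7 if d is on the change SD. Whether that carries the trial past 80% cannot be settled from the article. The group main effect, at 28% to 34% power, and the time main effect, which compares no arms, should not be offered as evidence of efficacy. The planned analysis is not invalid; this is a recommended improvement.

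**What to change.** In section 2.9, replace the ANOVA as the treatment test with this: for each score, fit a linear model of the 6-month value on group, with the baseline value of the same score as covariate, and report the adjusted group difference with its 95% confidence interval. Add that group and time main effects from any ANOVA that is still reported are not evidence of efficacy.

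State the sidedness of the test in the same revision. If a power figure is quoted for the adjusted model, state the assumed pre-post correlation and the SD to which 0.6 refers, and give the figure as a range.

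The cost is a change of wording and one degree of freedom per model. No further participants, visits or measurements are needed. If outcome data have already been analysed, report the change as made after the fact and show the planned interaction test beside it.

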Previous research has shown that natural reduced water can improve symptoms in patients with hyperlipidemia [6]. In addition, in animal experiments, continuous drinking of natural reduced water showed anti-obesity effects [7]. There is evidence in clinical surveys linking obesity (or metabolic diseases) to gut microbiota fluctuation. Moreover, Hita Tenryosui water is known to change gut microbiota in animal experiments [7]. On the other hand, natural reduced water increased the expression of aquaporin, a membrane protein that specifically allows water molecules to pass through [8]. Aquaporins in the rat kidney have also been shown to play an important role in body water homeostasis [9]. Therefore, we hypothesized that natural reduced water would change body composition, such as body fat and body water content.

In addition, it has been confirmed that natural reduced water suppresses mental anxiety in mice [10]. When mice were fed natural reduced water for 6 months, urinary 8-hydroxy-2′-deoxyguanosine and blood urea nitrogen levels, which are used as biomarkers to detect anxiety, decreased. Moreover, natural reduced water exhibited anxiolytic-like effects in the conditioned fear and elevated plus maze tests. Hita Tenryosui water (natural reduced water) contains a lot of active hydrogen and reduced free radical production [4]. Stress related to anxiety was reported to be associated with increased free radical production, which natural reduced water may suppress [11]. In a 4-week human intervention experiment, natural killer (NK) cell activity was significantly higher in the group receiving natural reduced water than in the group receiving tap water [8]. Other previous studies have examined the relationship between NK cell activity and depressive tendencies. NK cell activity was reduced in depressed patients with a hip fracture compared with controls at 6 weeks post-fracture. Serum cortisol levels were also elevated in depressed patients compared with those in non-depressed patients [12]. Therefore, we examined the relationship between natural reduced water and psychological functions such as anxiety or stress level.

Based on these previous studies, we hypothesized that the continuous consumption of natural reduced water may affect cognitive function, body composition, and psychological function, and we tested this hypothesis.

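### No primary outcome is named: the same ANOVA is applied to the scores of every measurement item, and the sample size is tied to none of them

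*Protocol article*

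**What the plan says.** The Introduction closes with one hypothesis that spans three domains: "we hypothesized that the continuous consumption of natural reduced water may affect cognitive function, body composition, and psychological function, and we tested this hypothesis". Section 2.1 describes the design as measuring cognitive function before and after six months, then gives cognition, body composition and psychological function side by side as the study's purpose.

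Section 2.7 lists eight instruments. Section 2.9 applies an analysis of variance with group and time as factors "to examine the relationship between the scores of each measurement item in the intervention and control groups". It calls only the later path analysis exploratory, and it states neither a significance level nor a rule for declaring success.

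The only alpha in the article is in section 2.8: "Assuming a significance level (α) of 5%, the effect size at 0.6", with power "of 80%, which are all “moderate” levels according to Cohen". From these, "the required number of participants was 34 in each group". Allowing for dropout gives "assuming a drop rate of 10%, would require approximately 38 participants, for a total of 76 recruits", and then "We added two more people to each group in case of unforeseen circumstances". No score is attached to the effect size.

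**The concern.** A sample size with one alpha, one effect size and one power describes a single comparison. The article never identifies that comparison, and then applies the same analysis to every score in three domains. As written, nothing says which result would decide whether the water improves cognition, or whether a result in one domain could stand in for a null result in another.

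The 5% in section 2.8 therefore does not describe the error rate of the trial's overall conclusion. A chance difference on one score could be reported as an effect on cognition, body composition or mood. The Discussion presents the water as a possible means of preventing dementia, so such a finding would carry weight. The choice also cannot be made credibly once results by group are known.

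**Working it through.** **1. The plan's own figure.** Inputs from section 2.8: alpha 5%, standardised effect 0.6, power 80%, equal groups. Formula: n per group = 2 × ((z_alpha + z_power) / 0.6)².

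- One-sided: 2 × ((1.645 + 0.842) / 0.6)² = 34.3; the t-test gives 35.0.
- Two-sided: 2 × ((1.960 + 0.842) / 0.6)² = 43.6; the t-test gives 44.6, so 45.

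The stated 34 is close to the one-sided figure only. The dropout step reproduces: 34 / 0.9 = 37.8, so 38, and two more make 40. None of these steps needs a particular score, and none is named.

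**2. How many scores.** From section 2.7:

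| Instrument | Named scores |
|---|---|
| MMSE | 1 |
| Trail Making, parts A and B | 2 |
| Digit Span, forward and reverse | 2 |
| Verbal fluency, category and letter | 2 |
| POMS 2 scales | 6 |
| PSS | 1 |
| SHS | 1 |
| Body water, fat, muscle | 3 |
| **Total** | **18** |

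One score per instrument would be 8. Cognition alone has 1 + 2 + 2 + 2 = 7.

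**3. Chance of at least one false positive, any direction.** Assumptions: no effect of the water, each score tested two-sided at 5%, and one test per score (group by time). For independent tests the chance is 1 − 0.95^k. For correlated tests it was computed from equally correlated normal statistics. The article gives no correlations, so a range is shown.

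| Common correlation | 8 tests | 18 tests |
|---|---|---|
| 0 | 34% | 60% |
| 0.3 | 30% | 51% |
| 0.5 | 25% | 40% |
| 0.7 | 19% | 28% |

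With 18 scores correlated 0.3 within cognition, 0.5 within mood and within body composition, and 0.1 between domains, the figure is 52%. With 0.7 within every domain and 0.1 between, it is 41%. Simulated t-tests on change with 34 per group gave 59%, 52% and 41% at correlation 0, 0.3 and 0.5, in line with the table.

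**4. Favourable direction only.** Each two-sided 5% test has a 2.5% chance of a false result in favour of the water. For 18 independent scores, 1 − 0.975^18 = 37%. At correlation 0.3, 0.5 and 0.7 it is 26%, 20% and 14%.

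**5. Power if a primary outcome is tested two-sided at 5%.** Taking 0.6 as the standardised difference in change, t-test power is 68% with 34 per group, 71% with 36 (40 less 10% dropout) and 75% with 40. Reaching 80% takes 45 analysed per group.

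**The case against.** The strongest reply is that this is a condensed article with no analysis plan at hand, and multiplicity handling is commonly left to that plan. This is right as far as it goes. A reader might infer that every one of 18 scores is certain to be tested at 5% with no error control. The article does not say so. The 5% appears only as a sample-size assumption, and silence on adjustment is not evidence that none is planned.

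The count is also open. Section 2.7 numbers eight items, and the article does not say whether Digit Span, fluency or POMS 2 will be analysed by part or in total. The reference in section 2.9 to scores favours counting parts, but does not settle it. So a flat statement that a useless water has a 40% to 60% chance of a positive result is too strong: it needs the larger count and correlations no higher than about 0.5.

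The harm described is a false claim of benefit, for which the favourable-direction figures are the relevant ones. Even these count all 18 scores, while section 3 predicts a direction for only some. Restricting to the 12 with a stated prediction (7 cognitive, body water, body fat, tension–anxiety, PSS, SHS) gives 1 − 0.975^12 = 26% if independent, 20% at correlation 0.3 and 16% at 0.5.

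It might also be tempting to count three F tests per score. The time effect is shared by both groups and says nothing about the water, so that adds nothing.

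What the reply does not remove is the missing primary outcome. The sample size depends on it, so it is a protocol decision. Reading cognition as primary from section 2.1 does not supply one, because seven cognitive scores remain and none is chosen.

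**Conclusion.** The point holds in this form: the article names no primary outcome, applies its main analysis to all scores in three domains without calling that analysis exploratory, and sizes the trial for a single unidentified comparison. That much rests on the text alone.

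The size of the resulting error depends on three assumptions: a 5% level per score, the number of scores analysed, and their correlation. The range is about 25% to 34% for 8 tests (correlation 0.5 down to 0) and 28% to 60% for 18 (0.7 down to 0). In the favourable direction it is about 14% to 37% for 18 tests. The exact value cannot be fixed from the article, but every figure in these ranges is well above the rate for one pre-specified comparison: 5% in either direction, 2.5% in the favourable one.

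**What to change.** Before unblinding, the sponsor should:

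- name one cognitive score of its own choice as the primary outcome, since section 2.1 makes cognition the design target;
- judge it at 5% on the group-by-time contrast only, that is, the between-group difference in change;
- tie the effect size in section 2.8 to that score and state whether the test is one- or two-sided;
- test the other scores with Holm's procedure within each domain, or report them as exploratory estimates with confidence intervals and no claims of significance.

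Most of this is wording, but it has two costs. Confirmatory claims on the other scores are given up under the exploratory option, and become harder to reach under Holm. The power must also be restated: with a two-sided 5% test and an effect of 0.6 it is about 68% with 34 per group and 75% with 40, not 80%. The sponsor would have to accept that power, justify a one-sided test, or plan for 45 analysed per group, which at 10% dropout means 45 / 0.9 = 50 recruited per group.

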## 3. Expected Results

We expect that continuous consumption of natural reduced water will improve cognitive function in the elderly. We also predict that body water content will increase and body fat percentage will decrease in the body composition of the participants. Furthermore, it is expected that anxiety and stress levels will decrease and subjective happiness will increase.

## 4. Discussion

Although various effects of natural reduced water (Hita Tenryosui water) have been studied in animal experiments, the relationship between natural reduced water and cognitive function in humans has not yet been investigated, so this research may be a novel study. There have been various studies on the prevention of dementia; this study examines the use of water, which is essential in daily life, as a potentially easy way to prevent dementia. On the other hand, one of the limitations of this study is that participants were free to consume water other than the daily 1 L of water in the study; thus, there could be effects from these other types of water, but this was true for both the intervention and control groups. Since this study was conducted on Japanese people, the applicability of this study to people of other nationalities needs to be verified in another study.

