### 2.4. Exclusion Criteria

Based on previous studies [13,14,15,16], the exclusion criteria for the participants included conditions related to electrolyte abnormalities (such as hyponatremia). The criteria were as follows:
(1)People with a current medical history:–Renal disease;–Cardiac disease;–Liver cirrhosis;–Syndromes of inappropriate antidiuretic hormone (SIADH);–Hypothyroidism;–Diabetes;–Hyperlipidemia;–Mental illness (polydipsia);–Vomiting or diarrhea.(2)People taking oral medications:–Antiepileptic drugs;–Antidepressants;–Diuretics;–Antihypertensive agents;–Antiarrhythmic drugs.(3)People with severe visual or hearing impairment;(4)People who have continuously consumed natural reduced water in the last year.

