### 2.5. Water Used for the Intervention

The natural reduced water used in this study was commercially available Hita Tenryosui water. For tap water, we used tap water from Oita Prefecture that had been boiled. Each type of water was poured into plastic bottles at the factory of Hita Tenryo-Sui Co., Ltd. The plastic bottles for both types of water were not labeled, and the same caps were used so that the participants themselves would not know which type of water they were drinking. Each bottle of water was delivered to the participant’s home on a regular basis.

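### No restriction on, or record of, outside natural reduced water is stated for the 6-month intervention, and free intake in both arms does not rule out dilution

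*Protocol article*

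**What the plan says.** The relevant statements in the protocol article are these.

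- Section 4 (Discussion): "participants were free to consume water other than the daily 1 L of water in the study". This is listed as a limitation, with the comment that "there could be effects from these other types of water, but this was true for both the intervention and control groups".
- Section 2.4 (Exclusion Criteria) excludes "People who have continuously consumed natural reduced water in the last year".
- Section 2.5 (Water Used for the Intervention): "The natural reduced water used in this study was commercially available Hita Tenryosui water".
- Section 2.6 (Protocol) describes an intake list for the 1 L of assigned water, and drops the data of people who take less than 90% of the total. It tells the natural reduced water group to abstain from that water between the post-intervention test and the follow-up test. It offers the water to the tap water group only after the post-intervention test.
- Section 2.8 (Sample Size) sets "the effect size at 0.6" and concludes that "the required number of participants was 34 in each group". No allowance for a weakened contrast is mentioned.

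**The concern.** The trial compares 1 L a day of natural reduced water with 1 L a day of tap water. By excluding recent continuous users, the plan accepts that natural reduced water from outside the study could disturb this comparison. That safeguard ends at entry. The only abstention rule printed applies to one arm and begins after the randomised comparison is over. For the 6 months in which the contrast is tested, the article states no corresponding rule and describes no record of other water.

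The answer given in section 4 deals with one threat only. Freedom shared by both arms, together with randomisation and blinding, makes a systematic difference in outside intake unlikely. Dilution is a different threat, because it can arise when outside use is the same in both arms. If it occurred, power would fall, and a small or null difference would be harder to interpret because outside use could not be reconstructed afterwards.

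**Working it through.** **1. What the stated rules cover, by period**

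| Period | Stated rule on natural reduced water from outside the study |
|---|---|
| Year before entry | Continuous use excludes (2.4) |
| 6-month intervention | None stated; other water is free (4); the list is described for the assigned water (2.6) |
| Post-test to follow-up | Test arm told to abstain; tap water arm may start (2.6) |

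**2. When shared freedom preserves the contrast**

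Let f(x) be the mean response to x litres a day of natural reduced water, with f(0) = 0. Let xT and xC be the outside intake of that water in the test and tap water arms. The group difference is f(1 + xT) − f(xC).

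- Outside water is ordinary water with no effect of its own: xT = xC = 0, so the difference is f(1), intact.
- Linear response with equal outside use: the difference is again f(1), intact.
- Linear response with unequal use: the difference is f(1) × (1 + xT − xC). It shrinks if controls drink more than the test arm, and grows in the reverse case.
- Response saturates at 1 L, and a share c of each arm drinks about 1 L outside: the test arm stays at f(1), the controls average c × f(1), and the difference is (1 − c) × f(1).

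Equal freedom is therefore compatible both with no loss and with a loss of the fraction c.

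**3. Reproducing the stated sample size**

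Inputs from section 2.8: α = 5% (sidedness not stated), effect size 0.6 (read as a standardised mean difference with SD 1), power 80%, two equal groups.

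n per group = 2 × [(z for α + z for power) / d]²

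- One-sided: 2 × [(1.645 + 0.842) / 0.6]² = 34.35, rounded up to 35. This is close to the stated 34.
- Two-sided: 2 × [(1.960 + 0.842) / 0.6]² = 43.6, rounded up to 44. This is not close.

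Of these two plain two-sample readings, only the one-sided comes near 34. A change-score analysis with an assumed pre-post correlation of 0.6 would also give about 34.9 two-sided, but the article states no correlation. Dropout: 34 / 0.9 = 37.8, rounded up to 38; adding 2 gives 40 per group.

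**4. Illustration of dilution**

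The article gives no rate of outside use, so c is an assumption, shown as a range. With d = 0.6 × (1 − c) and SD unchanged:

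Power = Φ(d × √(n/2) − z for α)

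Example, n = 34, c = 10%, one-sided: 0.54 × √17 = 2.227; 2.227 − 1.645 = 0.582; Φ = 72.0%.

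| Contrast lost (assumed) | d | Power at 34 per group, one-sided | Two-sided | n per group for 80%, one-sided | Two-sided |
|---|---|---|---|---|---|
| 0% | 0.60 | 79.6% | 69.6% | 35 | 44 |
| 10% | 0.54 | 72.0% | 60.5% | 43 | 54 |
| 20% | 0.48 | 63.1% | 50.8% | 54 | 69 |
| 30% | 0.42 | 53.5% | 41.0% | 71 | 89 |

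If all 40 per group were evaluable, one-sided power would be 77.9% at a 10% loss and 69.2% at a 20% loss. The extra recruits are planned for dropout and unforeseen events, not for dilution.

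**The case against.** The strongest reply is that the article never says controls could drink the test water. Section 4 speaks of other types of water, which most naturally means ordinary drinking water. Section 2.6 offers natural reduced water to the tap water group only after the post-intervention test, which suggests that earlier use was not intended. Instructions to participants, or a fuller intake list, may stand in the full protocol. All of this stands: a reader might infer that use of the test water by controls was permitted, or that outside use is certainly unrecorded, but the article supports only that no restriction and no record are stated.

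A reader might also infer that the plan regards the matter as harmless. It does not: section 4 calls it a limitation and concedes possible effects. The fair criticism is that the balance remark understates it.

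Nor does the article show that the difference must shrink. Section 2.6 gives a safety reason for choosing 1 L, with more having been used in earlier studies, so nothing indicates that the response is flat above 1 L. High outside use among controls may also be unlikely: they already receive study water at home, do not know which water it is, and were not recent continuous users. The upper end of the 10% to 30% range may therefore be remote.

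Finally, the gap between about 80% and about 70% power with no dilution at all comes from the unstated sidedness of the test. It is a separate matter and must not be counted as a cost of outside water.

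**Conclusion.** The point holds in a limited form. Other water is unrestricted in both arms, the test water can be bought, and for the randomised period the article states neither an abstention rule nor a record of outside natural reduced water. The remark that both groups had the same freedom answers systematic imbalance but does not rule out dilution.

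Dilution is conditional. It needs controls to drink natural reduced water together with a saturating response or greater outside use than in the test arm, or else other water that offsets the effect. Its size is unknown. The fall in one-sided power from 79.6% to between 72.0% and 53.5% rests on an assumed loss of 10% to 30% of the contrast, an effect size read as a standardised difference, and an unchanged SD. It is a sensitivity range and not a forecast. It does not support calling a null result uninterpretable; such a result would be harder to interpret. This is a cheap improvement to a limitation already disclosed, not a flaw that invalidates the design.

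**What to change.** - In section 2.6, ask both arms not to drink natural reduced or hydrogen water from outside the study during the 6 months. If the full protocol already says so, state it in the article.
- Add a line to the existing intake list for other water, by type and amount.
- Report outside use by arm with the results.
- Reword the limitation in section 4: shared freedom makes imbalance between the arms unlikely but may dilute the difference.

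The cost is one instruction and one line on a form that participants already complete, with slightly more burden for them. If the intervention has already ended, the last step is still possible, together with a plain statement of whether outside use was restricted or recorded.
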